# AIMS AND OBJECTIVES

We aim to assess the feasibility and acceptability of conducting an RCT to compare receiving ABC (an online-delivered, CBT, group-based, body image programme) alongside a psychoeducational body image booklet for women treated for breast cancer, with receiving the booklet only. Results will inform the design, management, and future delivery of an evaluation to assess effectiveness and cost-effectiveness in a definitive RCT.

Specific objectives are to:

- Establish appropriate, inclusive, and acceptable methods of participant recruitment, retention, and management procedures.
- Establish the feasibility and acceptability of quantitative data collection, including determining appropriate primary and secondary outcome measures.
- Adapt and test a measure of health and social care service use, to inform a future economic evaluation.
- Establish intervention adherence and acceptability (of online setting) among participants and ABC facilitators.

This study will examine uncertainties that need addressing before a definitive RCT:

- Recruitment processes and response rates: Responses from potential participants invited for randomisation and investigating reasons for declining.
- Intervention adherence and retention within the study: Percentage of participants completing each ABC session, reading the Macmillan booklet (in the control arm), and completing outcome measures at each assessment. This will additionally help calculate the sample size for the proposed follow-on RCT.
- Participants’ experience of randomisation to either the intervention or control arm and their experience of being in these arms.
- Participants’ responses and feedback to self-complete measures. This will determine suitability of the measures for an RCT.
- Adaptation and testing of a measure of health and social care service use: Assessment of comprehensiveness of the service use measure and acceptability of the measure to collect data for a health economic evaluation.

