The proposed secondary outcome measures undergoing consideration for a subsequent RCT will be assessed at all four timepoints, and are as follows:

- Hopwood Body Image Scale (Hopwood et al., 2001; Appendix 21)

A 10-item scale measuring body image in cancer patients. The scale includes measurement of affective, behavioural, and cognitive elements of body image. Participants rate each item on a 4-point scale.

- BREAST-Q: Sexual Well-Being Scale (Pusic et al., 2009; Appendix 22)

The BREAST-Q is a measure of quality of life and patient satisfaction comprising six subscales, of which we will use only the sexual well-being subscale. This six-item subscale asks participants to rate their feelings related to their sexual attractiveness, sexual confidence, and comfort during sex on 5-point scale

- - 1. **Health economic measures**

Measures for the economic evaluation include a measure of service use for the estimation of costs and two preference-based, generic measures of health-related quality of life as potential candidates for the estimation of quality adjusted life years (QALYs) suitable for cost-utility analysis in a definitive RCT. In addition, we have included a measure of functional impairment that may be suitable for cost-effectiveness analysis. The measures will all be completed by participants at baseline (T1; Week 1), three-month post-intervention (T3; Week 20), and six-month post-intervention (T4; Week 32) assessment points:

- Modified version of the Adult Service Use Schedule (AD-SUS; see Appendix 23 for T1 measure, Appendix 24 for T3 measure, Appendix 25 for T4 measure)

We have adapted a version of the AD-SUS that has been successfully used in depression-focused studies (e.g., Strauss et al, 2020, Richards et al 2016). The measure takes an NHS and social services perspective and has been adapted to ensure coverage of services relevant to women treated for breast cancer through a literature review (existing economic evaluations focused on this population), review of cancer-focused service use measures in the Database of Instruments for Resource Use Measurement (DIRUM; https://www.dirum.org/) and discussions with the team. At baseline, the ABC AD-SUS covers the last 3 months and at follow-up, the measure covers the period since the last assessment. We will test and further adapt the ABC AD-SUS to support the estimation of the cost of services used by participants in a future definitive RCT.

- EQ-5D-5L (Herdman et al., 2011; Appendix 26)

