The self-report outcome measures (K10, BAS-2, FACT-B: Breast Cancer Subscale, Hopwood Body Image Scale, and BREAST-Q: Sexual Well-Being Scale) are each well-established validated measures which will be scored according to the most appropriate guidelines. The design (pre- post- two arm parallel randomised controlled trial) and the selected measures are amenable to analysis using long-established statistical techniques. The analysis will proceed using the intention-to-treat analysis set with the statistician blinded to allocation. These analyses include:

- Descriptive statistics (including mean and standard deviation) by randomised arm at each time point (T1, T2, T3, and T4).
- Unadjusted statistical comparison between arms at each timepoint (T1, T2, T3, and T4) using the independent samples *t*-test with 95% and 80% confidence intervals and quantification of effect size using Cohen’s *d*. If statistical assumptions do not seem tenable, robust non-parametric bootstrap equivalent tests will be used.
- Adjusted statistical comparison between arms at each timepoint (T2, T3, T4) will be conducted controlling for commensurate baseline measures using ANCOVA (Analysis of Covariance) along with 95% and 80% covariate adjusted confidence intervals and quantification of effect size using partial eta -squared. If statistical assumptions do not seem tenable, robust remedies will be considered, including a baseline by randomised arm interaction effect, or homoscedasticity corrected robust standard errors (HC3) or the robust non-parametric bootstrap equivalent ANCOVA.
  1. **Heath economic evaluation**

The draft ABC AD-SUS (Appendices 23-25) will undergo testing for the following:

- Acceptability: This will be assessed via the proportion of participants completing the measure, percentage of missing items, and consideration of the clarity of any questions associated with missing data.
- Comprehensiveness: This will be assessed via open-ended questions included in the AD-SUS asking participants to report any ‘other’ services not reported elsewhere in the measure (missing items).
- Redundancy: This will be assessed through consideration of any service items included in the AD-SUS but not reported as being used by any participant (redundant items).

These results, plus feedback from participants, will inform a final version of the AD-SUS for a future definitive trial.

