**Please include all contacts, whether they took place in person, by telephone or online by video conference.**

|  | **Yes** | **No** | **If yes, please enter the total number of contacts you had in the last 3 months** |
| --- | --- | --- | --- |
| **General practitioner (GP)** |  |  |  |
| **Practice nurse (a nurse based in a GP surgery)** |  |  |  |
| **Cancer nurse/breast cancer nurse in the community (please exclude any contacts with a breast cancer nurse in hospital)** |  |  |  |
| **Any other nurse in the community, for example a district nurse, health visitor or midwife** |  |  |  |
| **Cancer support specialist/cancer support worker** |  |  |  |
| **Social worker, family support worker, or any other social services worker** |  |  |  |
| **Any therapist providing ‘talking therapy’, for example, cognitive behaviour therapy, counselling, mindfulness-based therapy, dialectical behaviour therapy, etc.** |  |  |  |
| **Excluding any contacts with therapists already reported in the previous question, any other mental health worker in the community, for example a psychiatrist, a Community Psychiatric Nurse (CPN), a Community Mental Health Team (CMHT) worker, etc.** |  |  |  |
| **Excluding any contacts already reported in previous questions, any other advice or support relating to cancer (either online, over the phone or in person) from a charitable organisation such as Macmillan Cancer Support, Maggie’s Centres, Penny Brohn, Breast Cancer Now, Keeping Abreast, Flat Friends, Look Good Feel Better, OUTpatients (formerly known as Live Through This), Switchboard Black Women Rising, etc.** |  |  |  |
| **Excluding any contacts already reported in previous questions, any other advice or support relating to mental health (either online, over the phone or in person) from a charitable organisation such as the Samaritans, MIND, Macmillan, etc.** |  |  |  |

| **Any other health or social care services in the community** | **Yes** | **No** | **If yes, please tell us what this service was** |
| --- | --- | --- | --- |
| **Have you used any other health or social care service in the community in the last 3 months?** |  |  |  |
| **Have you used any other health or social care service in the community in the last 3 months?** |  |  |  |
| **Have you used any other health or social care service in the community in the last 3 months?** |  |  |  |

1. **MEDICATION**

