We would like to know if you have been prescribed any medication by a doctor or other health professional for mental health or cancer-related reasons in the last 3 months. This might include, for example, medication for depression, anxiety, sleep disorders, etc, or hormone blocking medications.

For each medication category listed below, please tell us if you have been prescribed medication for this reason in the last 3 months by selecting ‘Yes’ or ‘No’.

Please ignore any over-the-counter medications (medications you can buy directly from a chemist/pharmacy that do not require a prescription).

| **Medication for:** | **For example:** | **Yes** | **No** |
| --- | --- | --- | --- |
| **Depression or**  **Anxiety** | Fluoxetine, Prozac, Sertraline, Lustral, Escitalopram, Cipralex, Citalopram, Cimpramil, Fluvoxamine, Faverin, Mirtazapine, Zispin, Venlafaxine, Efexor, Atomoxetine |  |  |
| **Sleep disorders** | Dexamphetamine, Dexedrine, Melatonin, Diazepine, Valium |  |  |
| **Attention Deficit Hyperactivity Disorder (ADHD)** | Methylphenidate, Ritalin, Equasym XL, Concerta XL, Medikinet XL, Dexamphetamine, Dexedrine, Intuniv, Lisdexamfetamine, Elvanse, Atomoxetine, Strattera, Guanfacine XR |  |  |
| **Hormone blocking therapy** | Tamoxifen, letrozole, exemestane, anastrozole, goserelin, zoladex, leuproreline, lucrin |  |  |

| **Any other prescribed medications** | **Yes** | **No** | **If yes, please tell us the name of the medication. If you are not sure of the name, please describe what the medication was for.** |
| --- | --- | --- | --- |
| **Have you been prescribed any other medication in the last 3 months?** |  |  |  |
| **Have you been prescribed any other medication in the last 3 months?** |  |  |  |
| **Have you been prescribed any other medication in the last 3 months?** |  |  |  |

AD-SUS designed by [name] at King’s College London. For further information please contact: King’s Health Economics, Institute of Psychiatry, Psychology & Neuroscience, King’s College London, [name]. Email: [[contact]](mailto:[contact])

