**Please include all contacts, whether they took place in person, by telephone or online by video conference.**

|  | **Yes** | **No** | **If yes, please enter the total number of contacts you had since you entered the ABC study approximately 5 months ago** |
| --- | --- | --- | --- |
| **General practitioner (GP)** |  |  |  |
| **Practice nurse (a nurse based in a GP surgery)** |  |  |  |
| **Cancer nurse/breast cancer nurse in the community (please exclude any contacts with a breast cancer nurse in hospital)** |  |  |  |
| **Any other nurse in the community, for example a district nurse, health visitor or midwife** |  |  |  |
| **Cancer support specialist/cancer support worker** |  |  |  |
| **Social worker, family support worker or any other social services worker** |  |  |  |
| **Any therapist providing ‘talking therapy’, for example cognitive behaviour therapy, counselling, mindfulness-based therapy, dialectical behaviour therapy, etc.**  ****If you are in the ABC therapy group, please EXCLUDE your use of the ABC therapy**** |  |  |  |
| **Excluding any contacts with therapists already reported in the previous question, any other mental health worker in the community, for example a psychiatrist, a Community Psychiatric Nurse (CPN), a Community Mental Health Team (CMHT) worker, etc.** |  |  |  |
| **Excluding any contacts already reported in previous questions, any other advice or support relating to cancer (either online, over the phone or in person) from a charitable organisation such as Macmillan Cancer Support, Maggie’s Centres, Penny Brohn, Breast Cancer Now, Keeping Abreast, Flat Friends, Look Good Feel Better, OUTpatients (formerly known as Live Through This), Switchboard Black Women Rising, etc.** |  |  |  |
| **Excluding any contacts already reported in previous questions, any other advice or support relating to mental health (either online, over the phone or in person) from a charitable organisation such as the Samaritans, MIND, Macmillan, etc.** |  |  |  |

1. **MEDICATION**

We would like to know if you have been prescribed any medication by a doctor or other health professional for mental health or cancer-related reasons in the last 5 months. This might include, for example, medication for depression, anxiety, sleep disorders, etc, or hormone blocking medications.

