**Please include all contacts, whether they took place in person, by telephone or online by video conference.**

|  | **Yes** | **No** | **If yes, please enter the total number of contacts you had since you last completed the ABC questionnaires approximately 3 months ago** |
| --- | --- | --- | --- |
| **General practitioner (GP)** |  |  |  |
| **Practice nurse (a nurse based in a GP surgery)** |  |  |  |
| **Cancer nurse/breast cancer nurse in the community (please exclude any contacts with a breast cancer nurse in hospital)** |  |  |  |
| **Any other nurse in the community, for example a district nurse, health visitor or midwife** |  |  |  |
| **Cancer support specialist/cancer support worker** |  |  |  |
| **Social worker, family support worker, or any other social services worker** |  |  |  |
| **Any therapist providing ‘talking therapy’, for example cognitive behaviour therapy, counselling, mindfulness-based therapy, dialectical behaviour therapy, etc.**  ****If you are in the ABC therapy group, please EXCLUDE your use of this therapy**** |  |  |  |
| **Excluding any contacts with therapists already reported in the previous question, any other mental health worker in the community, for example a psychiatrist, a Community Psychiatric Nurse (CPN), a Community Mental Health Team (CMHT) worker, etc.** |  |  |  |
| **Excluding any contacts already reported in previous questions, any other advice or support relating to cancer (either online, over the phone or in person) from a charitable organisation such as Macmillan Cancer Support, Maggie’s Centres, Penny Brohn, Breast Cancer Now, Keeping Abreast, Flat Friends, Look Good Feel Better, OUTpatients (formerly known as Live Through This), Switchboard Black Women Rising, etc.** |  |  |  |
| **Excluding any contacts already reported in previous questions, any other advice or support relating to mental health (either online, over the phone or in person) from a charitable organisation such as the Samaritans, MIND, Macmillan, etc.** |  |  |  |

1. **MEDICATION**

We would like to know if you have been prescribed any medication by a doctor or other health professional for mental health reasons since you last completed the ABC questionnaire approximately 3 months ago. This might include, for example, medication for depression, anxiety, sleep disorders, etc.

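### The AD-SUS comprehensiveness test in Section 7.3 relies on open 'other' questions that appear only in the baseline form, so as specified it cannot be run on the T3 or T4 data

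*Protocol*

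**What the plan says.** Adapting and testing a measure of health and social care service use is the third primary objective in the Trial Summary. Section 2 (Aims and Objectives) lists among the uncertainties to settle before a definitive trial: "Assessment of comprehensiveness of the service use measure and acceptability of the measure to collect data for a health economic evaluation".

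Section 7.3 turns this into tests on all three versions of the form: "The draft ABC AD-SUS (Appendices 23-25) will undergo testing for the following", followed by acceptability, comprehensiveness and redundancy. For comprehensiveness the method is stated: "This will be assessed via open-ended questions included in the AD-SUS asking participants to report any" other services that the measure does not cover.

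Section 5.6.4 sets the recall periods. The baseline form covers the preceding 3 months, and "at follow-up, the measure covers the period since the last assessment". Table 1 places the AD-SUS at T1 (Week 1), T3 (Week 20) and T4 (Week 32), and not at T2 (Week 9).

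Appendix 23 (T1) has two open blocks. One asks "Have you used any other health or social care service in the community in the last 3 months" and the other "Have you been prescribed any other medication in the last 3 months", each with three rows and a free-text column.

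**The concern.** Section 7.3 names Appendices 23-25 as the forms under test and says that the open questions are in the AD-SUS. That holds for one of the three forms. The two forms without the questions cover the time after baseline, which is the period a definitive trial would have to cost.

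The tests are also uneven. Redundancy (listed items that nobody uses) can be judged from all three forms. Missing items can be identified by the stated method only from the 3 months before baseline. A service or drug that women start to use after joining the study, and that is not on the list, would not be named on any AD-SUS form. This is not a detail that a statistical analysis plan could supply, because an analysis cannot recover answers to questions that were not asked.

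**Working it through.** No statistical formula applies. The check sets the three forms side by side and counts the weeks.

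**Open 'other' blocks by form**

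| Form | Other community services (free text) | Other prescribed medication (free text) | Open rows |
| --- | --- | --- | --- |
| T1, Appendix 23 | yes, 3 rows | yes, 3 rows | 3 + 3 = 6 |
| T3, Appendix 24 | none | none | 0 |
| T4, Appendix 25 | none | none | 0 |

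In Appendices 24 and 25 the community table ends with charity support for mental health and the medication section follows at once. The medication table has four closed categories and stops at hormone blocking therapy, followed directly by the designer's credit line. All other sections of the form (overnight stays, hospital appointments, A&E, ambulance, community contacts) are present at both follow-ups, so the absence does not look like a lost page.

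**What the remaining 'other' rows at T3 and T4 can show.** Both forms keep rows for overnight stays and hospital appointments for any other reason, other community nurses, other social services workers, other mental health workers, and other charity support for cancer or for mental health. Each takes a Yes/No and a number. None asks what the service was, so none can identify an item missing from the list.

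**Period without open questions.** From Table 1:
- T1 to T3: 20 − 1 = 19 weeks
- T3 to T4: 32 − 20 = 12 weeks
- Total: 19 + 12 = 31 weeks

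The open blocks cover the 3 months before baseline and none of these 31 weeks. The 31 weeks are the nominal schedule.

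**Two smaller points in the same forms**
- *Medication stem.* The T3 stem asks about medication "for mental health or cancer-related reasons in the last 5 months". The T4 stem asks about medication "for mental health reasons since you last completed the ABC questionnaire approximately 3 months ago", without cancer-related reasons, yet its table still lists hormone blocking therapy.
- *Recall anchor at T4.* The T4 form counts from the last completed ABC questionnaires, described as about 3 months earlier. T2 has questionnaires but no AD-SUS. A woman who completed T2 and missed T3 could count from Week 9 or from about 3 months ago. Under either reading her service use in Weeks 1-9 is not collected, and her reporting period is undefined.

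**The case against.** The strongest reply is that comprehensiveness is a property of the item list, and the listed services and medication categories are the same on all three forms. Baseline is completed before randomisation, so every randomised woman should meet the open questions, at the point when the sample is largest. Section 7.3 does not say that the test is repeated at each timepoint, and one sentence limiting it to T1 would remove the contradiction. This stands as a limit on severity. It does not remove the point: Section 7.3 names all three appendices, and baseline answers cannot show which unlisted services are used after baseline.

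A reader might also infer more than the documents support:
- *That unlisted follow-up use is entered as zero.* It is not asked about, which is different, and several catch-all rows still count part of it.
- *That the final AD-SUS would rest on baseline data alone.* Section 7.3 also draws on acceptability and redundancy, both of which can use T3 and T4 data, and on participant feedback. Appendix 10 at T4 and the completer interviews (Appendices 15 and 16) ask what other support was sought. They cover body-image support only and lie outside the AD-SUS, so they supplement the stated test without replacing it.
- *That a planned comparison of baseline with follow-up use is invalidated.* No such comparison is specified. Section 7.3 has service use summarised descriptively, and the recall periods differ by design.
- *That the recall windows are materially mis-stated.* The forms say approximately 5 and 3 months, and nearly all stems are tied to an event. Treating the approximations as exact would be unfair.

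On the T4 medication stem, the instruction to answer for each listed category still invites an answer on hormone blocking therapy, so the inconsistency is minor and no definite data loss follows.

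**Conclusion.** The mismatch between Section 7.3 and Appendices 24 and 25 is real and should be fixed. The comprehensiveness test, as specified, can be carried out on one of three forms. It covers the 3 months before baseline and none of about 31 post-baseline weeks, during which other community services and other prescribed medication are not asked about. It affects a primary objective, but it narrows the test rather than defeating it, because the baseline answers remain usable and the other evidence named in Section 7.3 is unaffected.

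Section 7.3 speaks of services. The medication gap is adjacent to the stated test, although it arises from the same omission. The conclusion assumes that the forms given to participants match the printed appendices.

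**What to change.** **Main change.** Copy the two open blocks from Appendix 23 into Appendices 24 and 25, reworded to each form's recall period. The cost is six optional rows per follow-up form and a form amendment. Version 3 of the protocol (Appendix 30) already changed the follow-up questionnaires, so there is a precedent. If the change is made while follow-up is under way, some participants will have completed the forms without the blocks. Record which version each participant completed, and report the comprehensiveness results with the number who were asked the open questions.

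**If the forms can no longer be changed.** State in Section 7.3 that comprehensiveness is assessed at T1 only, and limit the conclusion to services used in the 3 months before baseline. This costs one sentence but leaves post-baseline comprehensiveness untested by the stated method.

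**Minor, in the same amendment.** Make the T4 medication stem consistent with its table. Anchor the T4 recall to the date of the participant's last AD-SUS, inserted in the online form or printed on the paper one, so that women who missed T3 have a defined period.
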